#### Secondary study parameter(s)

The proportion of patients with a surgical site infection will be compared between groups using Pearson’s chi-squared test. Differences in the mean scores on the SF-12 and the NRS for pain and for cosmesis will be compared using the independent-samples t-test. Poisson regression will be used to compare the number of outpatient department visits, measured during the first 6 months post-operatively. All secondary parameters will be tested on the intention to treat sample, and are measured over the first 6 months after treatment.

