## Abstract

**Background:**

Seroma formation is a common complication after breast cancer surgery and can lead to delayed wound healing, infection, patient discomfort and repeated visits to the outpatient clinic. Mastectomy combined with flap fixation is becoming standard practice and is currently combined with closed-suction drainage. There is evidence showing that closed-suction drainage may be insufficient in preventing seroma formation. There is reasonable doubt whether there is still place for closed-suction drainage after mastectomy when flap fixation is performed.

We hypothesize that mastectomy combined with flap fixation and closed suction drainage does not cause a significant lower incidence of seroma aspirations, when compared to mastectomy and flap fixation alone. Furthermore, we expect that patients without drainage will experience significantly less discomfort and comparable rates of surgical site infections.

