## Objectives

### Research hypothesis

We hypothesize that flap fixation with closed suction drainage does not cause a significantly lower incidence of seroma aspirations when compared to flap fixation alone. We also expect that patients without drainage will experience less discomfort and will have comparable rates of surgical site infections.

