#### Secondary objectives

Assess whether patients with or without drainage after mastectomy experience more pain, experience different quality of life, undergo more invasive interventions related to seroma, develop more surgical site infections or require more unplanned visits to the hospital. Self-assessed cosmesis will also be evaluated.

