#### Secondary outcome measures

Assess:
Number of invasive interventions related to seroma or wound healing defined as: every aspiration of clinically significant seroma, incision and drainage of abscess or infected seroma and/or operative debridement of the wound.Surgical site infection (SSI) rate, defined as redness, pain, heat or swelling at the site of the incision or by the drainage of pus. Infection rate will be measured by A) the need for antibiotics, B) seroma aspiration due to infection or C) surgical drainage.Cosmesis assessed by the patient at every planned outpatient clinic visit. At these visits patients are asked to rate the cosmesis of the chest wall using a numeric rating scale (NRS) on a scale from 0 to 10.Quality of life measured using the SF-12 (Short Form) Health Survey. This is a 12-item questionnaire used to assess health related quality of life from the patient’s perspective. Two subscales are derived from the SF-12: the Physical Component Summary (PCS) and the Mental Component Summary (MCS) with a range from 0 to 100. A score of less than 50 means the patient scores lower than the general population and a score of more than 50 means the patient scores higher than the general population. Patients will be asked at baseline and at every postoperative planned outpatient clinic visit to fill in this questionnaire.The number of outpatient department visits, measured during the first 6 months postoperatively. This will be measured to see if patients have to come to the hospital more often due to seroma or seroma related complications.Wound pain and pain at the drain site measured by the patient using the NRS on a scale from 0 to 10 at the first postoperative outpatient clinic visit.

All outcome measures will be measured during the first 6 months postoperatively.

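### The plan expects comparable infection rates without a drain but analyses infection only with a test of difference, which cannot support that expectation

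*Protocol article*

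**What the plan says.** The article makes three statements about surgical site infection that bear on this point.

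- **Expectation.** Under Research hypothesis, patients without drainage "will experience less discomfort and will have comparable rates of surgical site infections". The Abstract, under Background, says the same: "patients without drainage will experience significantly less discomfort and comparable rates of surgical site infections".
- **Secondary objective.** Under Secondary objectives, the question is whether patients with or without drainage "develop more surgical site infections or require more unplanned visits to the hospital". This asks about a difference.
- **Analysis.** Under Secondary study parameter(s): "The proportion of patients with a surgical site infection will be compared between groups using" Pearson's chi-squared test. The section adds: "All secondary parameters will be tested on the intention to treat sample".

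For the primary outcome, seroma aspiration, the method is different. The Sample size section sets a 10-point non-inferiority limit. The section on primary study parameters compares the upper confidence bound of the difference in proportions with that limit. Neither section extends this to infection.

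**The concern.** The primary and infection expectations have the same form: leaving out the drain should not make things worse. For aspiration the article uses a method that can support such a statement, an upper confidence bound. For infection it names a test whose null hypothesis is no difference. Failing to reject that null is compatible both with equal rates and with a substantial increase that the trial was too small to detect.

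The Discussion says the results could lead to drains being omitted, so readers will look at infection when weighing that change. If the p-value is the only planned result, nothing in it separates rates shown to be close from rates too imprecise to tell apart.

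**Working it through.** **Inputs.** The Sample size section gives 112 evaluable and 125 enrolled patients per group, a 10% aspiration rate in both groups, a 10-point limit, 80% power and 10% drop-out. The article states no significance level for any test and no expected infection rate. I assume two-sided 0.05 for the chi-squared test and show a range of rates.

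**1. The plan's own figure.** n = 2 × 0.10 × 0.90 × (1.645 + 0.842)² / 0.10² = 111.3, so 112 per group; 112 / 0.9 = 124.4, so 125. This reproduces with one-sided 0.05. One-sided 0.025 gives 142 and does not. The sizing concerns aspiration only.

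**2. Power of the chi-squared test for a true doubling of infection.** Power = Φ[(d − 1.96·se₀)/se₁], where se₀ uses the pooled proportion and se₁ the separate proportions.

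For 5% versus 10% at 125 per group: se₀ = √(2 × 0.075 × 0.925/125) = 0.0333 and se₁ = √((0.05 × 0.95 + 0.10 × 0.90)/125) = 0.0332. Then (0.05 − 1.96 × 0.0333)/0.0332 = −0.46, and Φ = 0.32.

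| Drain vs drain-free | 112 per group | 125 per group |
|---|---|---|
| 2% vs 4% | 14% | 15% |
| 5% vs 10% | 29% | 32% |
| 10% vs 20% | 56% | 60% |
| 15% vs 30% | 77% | 81% |
| 20% vs 40% | 91% | 94% |

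Exact enumeration of the uncorrected test agrees within 2 points. For 80% power, 435 per group would be needed for 5% versus 10%, and 199 for 10% versus 20%.

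**3. One possible result: 18 of 125 without a drain, 9 of 125 with one (14.4% vs 7.2%).**

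- Difference: 7.2 points. Pooled proportion: 27/250 = 0.108.
- χ² = 0.072² / (0.108 × 0.892 × 2/125) = 3.36, p = 0.067.
- Wald 95% interval: 7.2 ± 1.96 × 3.90, which is −0.4 to 14.8 points.
- Score upper limit (Newcombe, from the Wilson limits of each proportion): 7.2 + √(7.22² + 3.37²) = 15.2 points.

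With 12 versus 6 of 125, p = 0.14 and the Wald upper limit is 11.2 points.

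**4. Where an observed doubling becomes significant.** With 125 per group, 20 versus 10 gives p = 0.052 and 22 versus 11 gives p = 0.040. With 112 per group, 18 versus 9 gives p = 0.065 and 20 versus 10 gives p = 0.0498. The switch lies at a drain-arm rate of about 9% (11/125 = 8.8%; 10/112 = 8.9%).

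**5. What an interval could show at this size.** If the observed rates are equal, the two-sided 95% upper limit is 1.96 × √(2p(1 − p)/n). That is 5.4 to 5.7 points at a 5% rate, and 7.4 to 7.9 points at 10%, for 125 and 112 per group.

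**The case against.** The strongest defence is that the test fits the objective as written. Secondary objectives asks whether more infections develop, and a chi-squared test answers that. The word comparable appears only as something the authors expect; the formal hypothesis is about aspiration. This stands for the difference question. It leaves the expectation, stated in both the Abstract and Research hypothesis, without an analysis that could support it.

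A reader might infer that the trial will declare infection rates comparable whenever p exceeds 0.05. The article does not say so. It gives a decision rule only for the primary outcome and states no level for secondary tests. The misreading is a risk that the wording leaves open, not a planned rule.

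A reader might also infer that the trial would probably miss a doubling of infections. That depends on an unstated rate. At a drain-arm rate of 10% or more, a true doubling is more likely detected than missed. The infection definition is fairly broad ("Infection rate will be measured by A) the need for antibiotics, B) seroma aspiration due to infection or C) surgical drainage"), so a low rate cannot be presumed.

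Nor does the article rank infection as the main safety outcome; it is one of several secondary measures. Part of it is already inside the primary comparison, because aspiration of infected seroma is among the criteria for a primary event. Infections treated only with antibiotics or by surgical drainage are not.

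Finally, an article need not carry every reporting detail, and the absence of an infection limit is not itself a fault. The point rests on what is stated: an expectation of similarity beside a test that cannot show it.

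**Conclusion.** The concern holds in a limited form. The chi-squared test answers the difference question in Secondary objectives but cannot support the expectation of comparable infection rates.

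If the test is two-sided at 0.05 and infection rates are low, the gap matters. A true doubling from 5% to 10% would be non-significant about 68–71% of the time, and from 10% to 20% about 40–45% of the time. A non-significant observed doubling is possible when the drain-arm rate is below about 9%, and the upper limit of the difference can then reach about 15 points. At rates of 15% and above, power for a doubling is about 77% or more and the practical concern shrinks.

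This concerns the analysis and reading of one secondary outcome. It does not affect the primary non-inferiority conclusion.

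**What to change.** Change the infection sentence under Secondary study parameter(s), or the matching text in the analysis plan, in four ways:

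1. Make the risk difference in surgical site infection (drain-free minus drain), with a two-sided 95% score interval on the intention-to-treat sample, the main result.
2. Keep the Pearson chi-squared p-value, for the difference question only.
3. State that a non-significant p-value will not be read as comparable rates.
4. State that any comparability statement rests on the upper limit of the interval. If the sponsor chooses to set a limit for this, it should be stated before results are seen.

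A formal infection limit and an added per-protocol infection analysis are options, not requirements. A limit would create a second non-inferiority question for which the trial was not sized. For example, with equal true rates of 5% to 10%, 80% power and an assumed 5-point limit, 235 to 446 per group would be needed at one-sided 0.05, and 299 to 566 at one-sided 0.025.

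The change needs wording only, with no extra patients or data. Its cost is that the trial may be unable to claim comparable infection rates, which reflects what its size can show.

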### Mastectomy with low vacuum drainage

In the group with closed suction drainage, one low vacuum drain will be placed in the mastectomy gutter, lateral to the pectoral muscle before flap fixation is performed. The drain is connected to a low suction drain bottle. Drain output will be recorded daily. Drain removal will be performed once daily output is below 50 mL or after a maximum of 48 h, irrespective of drain output.

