### Data collection

The baseline characteristics and demographics will be collected preoperatively after the patient has given written informed consent. In this session the first SF-12 Health Survey questionnaire will be completed by the patient, with or without guidance of a member of the study. At the planned postoperative outpatient clinic visits at 1 week, 6 weeks, 3 months and 6 months, the patients will fill in the SF-12 Health Survey and will be asked to report on the cosmesis and experienced pain. Physical examination will take place to evaluate the wound and the presence of clinically significant seroma.

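### SF-12 and cosmesis are compared by t-tests that leave out the collected SF-12 baseline and the four visits; the pain comparison does not say which score is tested, and its schedule conflicts.

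*Protocol article*

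**What the plan says.** The analysis is set in the protocol article under Secondary study parameter(s): "Differences in the mean scores on the SF-12 and the NRS for pain and for cosmesis will be compared using the independent-samples t-test". That section names no visit, no summary over visits and no covariate. It adds that all secondary parameters are tested by intention to treat and cover the first six months.

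The data behind the test are richer:

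- **SF-12.** Secondary outcome measures gives two component scores, physical (PCS) and mental (MCS), and states: "Patients will be asked at baseline and at every postoperative planned outpatient clinic visit to fill in this questionnaire". Data collection confirms that the baseline is taken in the preoperative session: "In this session the first SF-12 Health Survey questionnaire will be completed by the patient". Follow-up lists four visits: 1 week, 6 weeks, 3 months and 6 months.
- **Cosmesis.** "Cosmesis assessed by the patient at every planned outpatient clinic visit", so four scores and no baseline.
- **Pain.** Secondary outcome measures defines this outcome as "Wound pain and pain at the drain site measured by the patient using the NRS", scored at the first postoperative clinic visit. Table 1 has one row, wound pain, marked at 1 week only. Data collection says that at all four visits patients "will be asked to report on the cosmesis and experienced pain". In the drain-free group no drain is placed (section Mastectomy without low vacuum drainage).

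**The concern.** The protocol asks patients for an SF-12 before surgery and then states a comparison that does not use it. It collects SF-12 and cosmesis four times and states a two-sample test without saying which of the four scores, or what combination of them, enters it. The expected benefit of leaving out the drain is less discomfort, so these secondary outcomes carry the positive side of a non-inferiority trial. An imprecise comparison could miss a real difference.

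Pain has two further problems. The outcome names two scores and the analysis speaks only of one NRS for pain. One of those scores cannot exist in the drain-free arm. The sections also disagree on when pain is asked, so it is unclear whether there is one pain score per patient or four.

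**Working it through.** **The plan's own figure.** The article gives a sample size for the primary outcome only. With 10% aspirations in each group, a 10-point margin and 80% power, n = 2 × 0.10 × 0.90 × (1.645 + 0.842)² / 0.10² = 111.3, so 112 per group. With 10% drop-out, 112 / 0.90 = 124.4, so 125. Both match the Sample size section, at a one-sided alpha of 0.05 that is inferred because the article states none. This figure says nothing about SF-12, cosmesis or pain. It only supplies the evaluable number, 112 per group, used below.

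**Inputs that are assumed.** The article gives no SD or correlation for these scores. Results are therefore in SD units, with a correlation ρ of 0.3, 0.5 or 0.7 between any two SF-12 assessments including baseline (and between any two cosmesis visits), equal variances, and two-sided 5% tests.

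**Baseline adjustment at one visit (SF-12).** ANCOVA multiplies the variance of the treatment difference by 1 − ρ². To match its precision with 112 per group, a plain t-test needs 112 / (1 − ρ²) per group.

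- ρ = 0.3: factor 0.91, variance down 9%, 112 / 0.91 = 123
- ρ = 0.5: factor 0.75, down 25%, 112 / 0.75 = 149
- ρ = 0.7: factor 0.51, down 49%, 112 / 0.51 = 220

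The factor left at ρ = 0.7 is 0.51, so the variance removed runs from 9% to 49%; 51% is the share that remains.

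**Use of all four visits.** For the average of four visits the factor is (1 + 3ρ)/4 without baseline, and (1 + 3ρ)/4 − ρ² with baseline. The difference detectable at 80% power is (1.960 + 0.842) × √(2 × factor / 112). Values below are for ρ = 0.3 / 0.5 / 0.7.

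| Analysis | Variance factor | Detectable difference (SD) | Power for 0.3 SD |
|---|---|---|---|
| t-test, one visit | 1 | 0.374 | 61% |
| ANCOVA, one visit (SF-12) | 0.91 / 0.75 / 0.51 | 0.357 / 0.324 / 0.267 | 65 / 74 / 88% |
| Mean of 4 visits, no baseline (cosmesis) | 0.475 / 0.625 / 0.775 | 0.258 / 0.296 / 0.330 | 90 / 81 / 72% |
| Mean of 4 visits, with baseline (SF-12) | 0.385 / 0.375 / 0.285 | 0.232 / 0.229 / 0.200 | 95 / 96 / 99% |

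The last two power rows assume that the difference is 0.3 SD at every visit. If it is confined to the early visits, averaging dilutes it and a named early visit is the better contrast.

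**Pain, side by side.** No arithmetic applies.

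- Which score: the outcome definition names wound and drain-site pain, Table 1 names wound pain, and the analysis section names neither.
- When: the outcome definition and Table 1 give the first visit only, while Data collection gives four visits.
- In which arm: wound pain exists in both arms, drain-site pain only where a drain was placed.

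**The case against.** The strongest reply is that the t-test is not wrong. Under randomisation it is valid at a single visit, and equally on each patient's average over visits. Omitting the baseline costs precision, not validity. The choice of visit for a secondary outcome is often left to a statistical analysis plan, which is not shown. All of this stands. What remains is that the article itself names the test, and that test makes no use of a baseline the trial collects. If the mean scores were read as per-patient averages, the four visits would be used, but the baseline would still be left out.

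Several stronger readings are tempting, and the article does not support them:

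- **That drain-site pain is tested between arms.** The analysis section does not say so, and Table 1 lists wound pain alone. The supportable point is that the tested score is not identified.
- **That drain-site scores would be imputed in the drain-free arm.** The Statistical analysis section says the imputation method will depend on why data are incomplete. Nothing there treats a score that does not apply as missing.
- **That every score will be tested at every visit, with a large chance of a false positive.** No section plans separate tests by visit.
- **That pain is measured too late to show a difference.** Drains come out "after a maximum of 48 h, irrespective of drain output" at the latest and the first pain score is at 1 week, about 5 days later. The article does not show that a difference has gone by then. An earlier score would be a new measurement, not an analysis choice.
- **That the repeated-visits complaint covers pain.** Under the outcome definition and Table 1, pain is scored once and an independent-samples t-test is an ordinary choice.

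**Conclusion.** The point holds as a loss of precision and a lack of definition in secondary outcomes, not as an invalid test. For SF-12, leaving out the baseline forgoes a variance reduction of 1 − (1 − ρ²) = ρ², which is 9% at ρ = 0.3 and 49% at ρ = 0.7 (remaining variance 91% to 51%). The 112 evaluable patients per group would then be worth about 123 to 220 under a plain t-test. The range rests wholly on the assumed correlation; the direction does not. For cosmesis there is no baseline, and the gain comes only from using the four visits. It shrinks as the visits become more correlated.

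For pain, the compared score is not identified, and the schedule is contradictory: once according to Secondary outcome measures and Table 1, four times according to Data collection. None of this touches the primary non-inferiority conclusion. The changes should be made because they are cheap and the comfort outcomes matter to the trial's argument.

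**What to change.** - **SF-12.** Analyse PCS and MCS each by a mixed model for repeated measures with treatment, visit, treatment-by-visit and baseline score, or by ANCOVA at a named visit. Name one visit or the average over visits in advance as the single contrast.
- **Cosmesis.** Use the same model without the baseline term, again with one contrast named in advance.
- **Pain.** State that wound pain is compared between arms, and report drain-site pain descriptively in the drain arm only.
- **Pain schedule.** Reconcile Secondary outcome measures, Table 1 and Data collection. If pain is kept at one visit, the planned t-test can stay for wound pain. If it is collected at four, use the cosmesis model.

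The cost is wording in the protocol or analysis plan and a slightly longer model. The SF-12 and cosmesis changes need no new data, visits or patients. Settling the pain schedule may need a formal amendment if it changes what is collected, as the Ethics and dissemination section requires for changes that may affect conduct.

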### Monitoring

No formal data monitoring committee was formed as the expected risk for participants and for data collection and processing is minimal. However, the trial will be periodically monitored by an external, independent monitoring organ (CTCM, Clinical Trial Center Maastricht) to evaluate trial conduct, such as quality and completeness of the data, patient follow-up, and identify if timely adjustments need to be made. Adverse events are defined as any undesirable experience occurring to a subject during the study, whether or not considered related to the trial procedure. All adverse events from grade 3 or higher according to the Common Terminology Criteria for Adverse Events grading (CTCAE-grading, Version 4.0, 2009) which occur within 6 months postoperatively reported by the subject or observed by the investigator or his staff will be recorded. An adverse event that meets the criteria for a serious adverse event (SAE) will be reported by the investigator to the accredited medical-ethical committee that approved the protocol according to guidelines.

### Ethics and dissemination

The study will be conducted according to the principles of the Declaration of Helsinki (Version 2008, December 2018) and in accordance with the Medical Research Involving Human Subjects Act (WMO) and other guidelines, regulations and Acts. All eligible patients will be informed about the study in the outpatient clinic as soon as the indication for mastectomy has been made. They will be informed by their surgeon and will receive a document with information regarding the study as well as an informed consent form. Written informed consent will be obtained before patients are scheduled for surgery. Subjects can leave the study at any time for any reason if they wish to do so without any consequences. Any amendments to the study protocol, which may impact the conduct of the study, will require a formal amendment to the local research ethics committee. Publications will follow international guidelines: CONSORT Statement. The results of the scientific research will be submitted to peer-reviewed journals and disclosed unreservedly.

